### 4.2 Message Transmission Experiment

During the last class of the course, five students were selected to read out loud their speech in front of their classmates and two guests. The guests were two first-year students not enrolled in the course, who have previously display little or no knowledge regarding palliative care in an assignment delivered for another university course. After hearing all the speeches, they were asked to define palliative care (S2 File). One of them defined palliative care as "a medical treatment intended for patients with a terminal illness with the aim of reducing their suffering as much as possible". The other one wrote that palliative care "is a special care that focuses on people who do not have the possibility of being cured of their illness. They try to support, both focused on the disease and psychological consequences, to the patient and the family".

Two lessons can be drawn from this experience. The first one is that the students were able to learn the basics of rhetoric from the four-hour seminar. The speeches written for the experiment were well structured and clearly expressed the concepts that the students had learnt during the course. The second one is that the speeches showed signs of being effective in conveying the concepts learnt throughout the course to the guests. The guests, who presumably knew little or nothing about palliative care prior to the experience, provided an acceptable definition of palliative care after hearing the speeches. Thus, the students of the course showed their ability to communicate and retransmit the palliative care message to their peers.

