### 2.2 Why university students from degrees unrelated to the health sector

In a health communication campaign, a desirable outcome is for the target audience to become an ambassador of the cause. Ambassadors, otherwise known as influencers, are people that can exert interpersonal influence or help reform the environmental condition that shapes the behaviors of the segment to be changed [24]. Creating ambassadors have two advantages. Firstly, they can customize the message to the needs and values of their peers [24]. Peer to peer communication has been proven to facilitate health messaging, because fellow community members are both trusted and relatable, and able to express information in an understandable and significant way [25]. Secondly, ambassadors are likely to respond to negative behaviors of those they are attempting to influence [24]. This type of engagement provides opportunities for giving instant feedback, having open dialogues, and answering questions immediately [26].

Moreover, as the issue of palliative care in the academic curricula of health-related degrees is already being tackled [27, 28], the aim of this course is to reach students belonging to areas of expertise outside the sector. Considering the two previous advantages, students with different backgrounds and areas of expertise are an ideal group to create ambassadors, as the variety of backgrounds will allow the palliative care message to be disseminated beyond the field of health. The social intervention proposes to reach the students through the Core Curriculum: an initiative designed to offer students from a wide range of degrees an integral education in core areas of study [29, 30]. Aligned with that objective, the Core Curriculum course Care and Society seeks to convey to the university students the value of caring for others within society.

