### 3.4 Moments of evaluation

The evaluation will assess the capacity of the course to turn students into ambassadors that can change the framework of the discussion in society. We understand as ambassadors the students who demonstrate: (1) an adequate degree of understanding of the concept of palliative care, (2) a positive attitude towards the social problem, (3) the ability to communicate the message of palliative care and (4) to retain the knowledge five months after taking the course. The overall assessment of the course will focus on four moments of evaluation (Fig 3).

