#### 3.4.3 Moment 3: Final assessment

The final two classes in the course contemplate a seminar where students will learn the basics of Rhetoric. They will write a speech, applying the knowledge of palliative care acquired during the course and the resources given throughout the seminar. The speeches will be sent to and graded by the professor, who will forward them to the research team to be analyzed accordingly. The teacher will then proceed to select the five best speeches for a Message Transmission Experiment. For this experiment, five selected students will deliver their speech in front of first-year students not enrolled or related in any way to the course. Following the speeches, the first-year students will fill out a questionnaire to assess their understanding of palliative care after the experience.

Additionally, prior to the last day of class, students will turn in a written reflection regarding the Module III experience. This material will also be analyzed for the research with the prior written consent of the students. After the class is over, students will receive the link to answer the last PCKQ and TECA. Participants will also receive a link to provide feedback on the course through a satisfaction and commitment questionnaire that includes an open question and a learning commitment regarding an attitude change: "After what you have learned in this course, what do you intend to change in your attitude in the coming months to enhance the palliative care message?".

Lastly, all the students and teachers of Care and Society will be invited to participate in a focus group to evaluate the overall experience in this course. The first five students who respond to this request will be selected. The purpose of this focus group is not to evaluate the knowledge of the participants, but to discuss the strengths and weaknesses of the methodology, the content and other aspects of the course. The focus groups will later be transcribed, and thematic content analysis of the material will be carried out.

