## 4. Preliminary results

The first edition of Care and Society took place from January to May 2022. The course had 29 students enrolled. For the preliminary results, we compared the PCKQ answers of the participants throughout the course. We also assessed the results of the Message Transmission Experiment, and we obtained an initial overview of the recurring themes of the focus group.

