### 5.1 Research question 1: Is educational innovation a suitable solution to the communication necessities of palliative care?

We believe that this approach is innovative as it averts the usual health promotion programs, in which the information moves on a one-way flow from the sender to the recipients and is heavily dependent on the media as a channel [9, 24]. This social intervention shifts the trajectory in the dissemination of palliative care knowledge to society. Rather than transferring knowledge on a hierarchical basis, it is a designed to be an extended experience that allowed students to witness what care looks like and have dialogues with professionals dedicated to caring.

By doing so, not only do we involve the students in their own learning, but we also provide them with the opportunity to redirect and adapt the syllabus to fit their needs. We thus ensure that students value their learning, which may result in said learning becoming perdurable and worthy of being retransmitted. Educational innovation seems to be a tailored solution to the communication necessities of palliative care, as it strives to leave a long-lasting impression on students, ensuring that the palliative care message is well embedded on the recipients.

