### 5.2 Research question 2: Can students help amplify the palliative care message?

This project perceives students of the Core Curriculum who are not in the health sector as potential re-transmitters of the palliative care message to society. If the information learnt through the course resonates with the students, they can potentially serve as a conduit to amplify the palliative care message as a result of the students’ high connectivity [24, 33]. High connectivity, or the ability to bridge multiple groups because of the formation of weak-tie relationships, allow the students to take what they have learnt in the course and share it with a wide variety of different audiences [33, 34]. Not only they may share it with other students in their degrees who didn’t enroll in this optative, but also with their family, friends and acquittances outside of the university environment.

Thus, we believe Care and Society used education as creative outlet that utilized rapid testing of multiple tools to create palliative care ambassadors in society. And we are also confident that these ambassadors are potential seeds of change, as they will be able both to send the message to multiple recipients and to react directly and immediately if they witness an incorrect portrayal of palliative care in their day-to-day life [25, 35]. This might potentially change the public opinion on palliative care in the long run.

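### The only performance test of communication is a prepared speech read by five selected students, so it supports neither the conclusion about all the course's students nor the confidence that they will correct wrong portrayals on the spot

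*Protocol article*

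**What the plan says.** Section 3.4 of the protocol article lists four marks of an ambassador. The third is "3) the ability to communicate the message of palliative care".

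Section 3.4.3 sets out the test. Every student writes a speech, which the professor grades and forwards to the research team. Then: "The teacher will then proceed to select the five best speeches for a Message Transmission Experiment". The outcome is measured on the listeners: "Following the speeches, the first-year students will fill out a questionnaire to assess their understanding of palliative care after the experience".

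Section 4.2 reports the test as run: "five students were selected to read out loud their speech in front of their classmates and two guests". The two guests each wrote a definition, and the article judged both acceptable. The section closes by crediting the course's students, without qualification, with a demonstrated capacity to pass the message on to peers.

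Two other places describe a broader ability. Section 2.2 justifies the choice of target group partly by the openings that ambassadors have for "having open dialogues, and answering questions immediately". Section 5.2 states confidence that the ambassadors will be in a position "to react directly and immediately if they witness an incorrect portrayal of palliative care in their day-to-day life".

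Section 3.4.4 plans a further assessment five months after grades are published. A questionnaire asks for an example of the attitude change, and interviews ask whether the student has passed the message on. Section 7 expects this to shed light on students' initiative when palliative care is misrepresented.

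**The concern.** Delivering a text that was written in advance, graded and picked as one of the five best is one skill. Answering a peer's unexpected question, or correcting a wrong statement when it is made, is another. A student may have the first without the second. The described test observes only the first, and only in students selected for doing it well.

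Two inferences are at stake. One is from five chosen speakers to the students of the course. The other is from prepared delivery to immediate reaction, which section 2.2 makes part of the reason for training ambassadors at all. If the same test goes unchanged to other universities, later editions will also have no observation of the second ability.

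**Working it through.** The article states no sample size, error rate or effect size that bears on this point, so there is no figure to reproduce. The check sets claim against evidence.

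**Inputs**
- Enrolled (section 4): "The course had 29 students enrolled".
- Speakers: 5 (sections 3.4.3 and 4.2).
- Guest listeners: 2 (section 4.2).
- Selection: by the teacher, on quality of the speech (section 3.4.3). Section 4.2 says only that five were selected, so I assume the planned rule was followed.

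**Step 1: coverage.** 5 / 29 = 17.2%. The remaining 29 − 5 = 24 students were not observed delivering the message to a guest. Because the five are the best by design, their result cannot be read as an average for the class.

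**Step 2: what the format can show.**
- *Prepared delivery:* observed for five speakers, through the definitions of two guests.
- *Answering an unplanned question:* neither the plan nor the report of the experiment describes one.
- *Correcting a misconception:* neither describes one.

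**Step 3: does another instrument fill the gap?**
- *Written speeches of all students (section 3.4.3):* these extend the data beyond the five, but they are still prepared text.
- *Escape Room debriefing (section 3.4.2) and focus group (section 4.3):* both are interactive, but the first serves teaching purposes and the second reviews the course. Neither tests a student explaining or correcting the message to a lay peer.
- *Moment 4 questionnaire and interviews (section 3.4.4):* these record what students say they did. They can inform on occurrence and initiative, but not on whether a reply was correct.

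**Step 4: claim against evidence.**
- *Section 4.2, students of the course can pass the message on:* supported at most for five selected speakers with a prepared text.
- *Section 5.2, ambassadors will react directly to wrong portrayals:* no pilot observation bears on it, and no planned instrument observes the skill.
- *Section 7, only some students seemed able to explain palliative care to the guests:* consistent with the evidence, and narrower than section 4.2.

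**Illustration.** One guest's definition after the speeches still tied palliative care to terminal illness, the idea that section 4.1 reports as typical of students' answers before the course. The described procedure gave no speaker an occasion to take that up.

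**The case against.** The strongest reply is that the experiment does what it was set up to do. The third criterion names communication of the message and says nothing of dialogue or rebuttal. Speaking to listeners thought to know little, then asking them for a definition, is a relevant if small test of that. The passage on open dialogue in section 2.2 is a cited general rationale, not a reported result. Section 5.2 is worded as an expectation, and both the abstract and section 7 defer the ambassador verdict to the mid-term results. Section 7 also concedes that the assessment of message transmission needs more work.

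Much of this stands, and it rules out several stronger readings that a reader might infer:

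- *That the article claims the experiment demonstrated dialogue or immediate reaction.* It does not. Section 4.2 speaks only of communicating and passing on the message. The fault in section 5.2 is that the stated confidence has no tested support.
- *That the test contradicts section 5.1*, where the approach is called innovative because "it averts the usual health promotion programs, in which the information moves on a one-way flow from the sender to the recipients". That contrast concerns how the course teaches its students. It does not govern how students must later address peers.
- *That communication is assessed nowhere else.* Moment 4 addresses retransmission and, according to section 7, advocacy, though by self-report.
- *That no student took part in any two-way exchange, or that the audience was silent.* The focus group was interactive, and the article simply describes no questions from the audience.

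An interval for two acceptable definitions out of two would add nothing. Both guests heard the same five speeches, and the issue is the format rather than precision.

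The reply does not remove the narrower point. Deferring the verdict to Moment 4 does not help where Moment 4 cannot observe the skill. The concession in section 7 concerns how efficiently the message is transmitted and what recipients knew beforehand, so acting on it would leave the prepared format as it is.

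**Conclusion.** The point holds in limited form. The experiment supports at most that five students, 17% of those enrolled and chosen for the best speeches, can deliver a prepared message. It does not support the unrestricted conclusion in section 4.2 about the students of the course. It also gives no support to the confidence in section 5.2 about immediate reaction to incorrect portrayals.

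This rests on two assumptions: that the five were chosen as section 3.4.3 plans, and that no unscripted exchange was part of the experiment, since none is described. If there was one and it was recorded, the second part of the conclusion would need to be looked at again.

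The matter should be corrected but does not undermine the pilot. The experiment remains a reasonable small test of prepared delivery, and the article's overall conclusion is already more cautious than section 4.2.

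**What to change.** 1. **Section 4.2:** limit the conclusion to prepared, one-way delivery by the five selected speakers, in line with the more careful wording of section 7.
2. **Section 5.2:** state that the ability to react at once to a wrong portrayal has not been tested.
3. **Section 3.4.3, next edition:** after each speech, have a guest put one unscripted question and one common misconception to the speaker, who answers without notes. Transcribe the answers and code them for correctness. Report the speech result as prepared delivery, and base any claim about dialogue or correction on the unscripted part alone.

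With five speakers and two prompts each, this gives 5 × 2 = 10 short answers. At an assumed one minute per answer, that is about 10 minutes of the same class, plus a little coding. The other cost is a narrower claim for the present pilot. The change fits the aim in section 3.2 of refining the assessment techniques before other universities use the course. Other interactive tasks with a scored response would also serve.

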#### 3.4.1 Moment 1: Initial assessment

In Moment 1, one week before the beginning of the course, students will receive an email inviting them to participate in the study. The invitation will have three links: one to the initial Palliative Care Knowledge Questionnaire (PCKQ), another to a Cognitive and Affective Empathy Test (TECA), and the last to a consent form for recontact. The initial PCKQ is meant to examine participants previous knowledge on palliative care. If any student shows a formidable knowledge on the topic, they will not be excluded from the study. Their performance will simply be recorded, and any improvement will be taken into consideration.

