#### 3.4.2 Moment 2: Learning assessment

Following the end of Module I, students will receive links to the PCKQ and TECA of Moment 2. Furthermore, to evaluate Module II for teaching purposes, a ten-minute debriefing will be recorded at the end of the Escape Room. With their written consent, transcripts of this recording will be used to help analyze the data.

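### The pilot credits the four-hour seminar with teaching rhetoric, but students' communication was not measured before it, so the speeches show attainment and not learning

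*Protocol article*

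**What the plan says.** Section 3.4 sets out to assess whether the course can turn students into ambassadors. It lists four things an ambassador demonstrates, the third being "the ability to communicate the message of palliative care".

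The instruments are then given moment by moment:

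- **Moment 1 (section 3.4.1):** a knowledge questionnaire (PCKQ), an empathy test (TECA) and a recontact form. On the first, "The initial PCKQ is meant to examine participants previous knowledge on palliative care".
- **Moment 2 (section 3.4.2):** "students will receive links to the PCKQ and TECA of Moment 2", plus a recorded debriefing after the Escape Room, made to evaluate Module II for teaching purposes.
- **Moment 3 (section 3.4.3):** "The final two classes in the course contemplate a seminar where students will learn the basics of Rhetoric". Of the students it then says: "They will write a speech, applying the knowledge of palliative care acquired during the course and the resources given throughout the seminar". For delivery, "The teacher will then proceed to select the five best speeches for a Message Transmission Experiment".

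Section 4.2 reports the pilot and draws as its first lesson: "The first one is that the students were able to learn the basics of rhetoric from the four-hour seminar". The support offered is that the speeches had a good structure and expressed the course concepts clearly.

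**The concern.** To say that students learned something from a seminar is to claim a change and to name its cause. A description of work produced after the seminar gives a level only. Participants are in their second or a later year of university and come from schools that include Education and Business (section 3.3). Some may already have been able to write a structured speech, and nothing in the plan would reveal it.

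The same gap touches criterion 3. Turning students into ambassadors implies movement from a starting point. Knowledge and empathy are measured from Moment 1, but communication has no starting point. The course is to be repeated over three years and taken to other universities (section 3.2). An unsupported statement about which component worked could therefore shape later editions.

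**Working it through.** The protocol states no sample size, power or effect figure that bears on this point. The check is a trace of what was measured and when, with simple counts.

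**1. Communication measures before the seminar.** Moment 1 has none and Moment 2 has none. The first is the Moment 3 speech, which uses the seminar's resources and so cannot precede it. Before-and-after pairs: 0, against a possible 25 who accepted to participate (section 4.1) or 29 enrolled (section 4).

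**2. Other student output that might serve as a baseline.**

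- *The PCKQ open question (section 4.1).* Students defined palliative care in their own words, with 12 questionnaire respondents at Moment 1 and 25 at Moment 2. These are relevant texts, but they were read for conceptual content and not for how well the message was conveyed. At Moment 3 the item was replaced by one asking what message the student would take away, so the definition has no post-seminar counterpart.
- *The Escape Room debriefing (section 3.4.2).* It precedes the seminar but is not described as a measure of communication.
- *The Module III reflection (section 3.4.3).* It is due before the last class. Whether it precedes the seminar is not stated, and it is not described as a measure of communication.

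**3. Any other comparison.** Section 6 states that there was no control group, so no untaught students can stand in for the missing starting level.

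**4. Which speeches the lesson rests on.** Section 4.2 does not make clear whether the judgement covers all speeches or only the five delivered. If only the five, they are 5/29 = 17% of those enrolled or 5/25 = 20% of participants. Under section 3.4.3 they are the teacher's choice of the best, so good structure is partly the reason they were chosen.

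**5. Whether the authors acknowledge the gap.** Section 6 covers the control group and the code system. Section 7 asks for a better assessment of the recipients' prior knowledge. Neither mentions the speakers' starting ability.

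**The case against.** The strongest reply is that criterion 3 describes an end state. Section 3.4 speaks of students who demonstrate the ability, and an end-of-course task can show whether they do. This stands. A reader might infer that criterion 3 cannot be evaluated at all, or that it rests on the speech alone. The documents support neither reading. The Moment 4 interviews (section 3.4.4) ask whether students have passed the message on, and section 7 expects firmer results on communication from that assessment. Moment 4 cannot, however, recover a level from before the seminar.

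A second reply is that rhetoric is not criterion 3. It is a teaching outcome of Module IV (section 2.3.4), while the criterion concerns conveying palliative care. That also needs content knowledge, which does have a Moment 1 measure. This stands in part: prior skill in speech writing bears mainly on the rhetoric sentence. A reader might also infer that nothing relevant was written before the seminar. The PCKQ definitions show otherwise, although they were not scored as communication.

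Third, the results are labelled preliminary, section 7 is hedged, and neither the abstract's conclusion nor section 7 repeats that rhetoric was learned. This limits the weight of the point. It does not rescue the sentence, which is unhedged where it stands.

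**Conclusion.** The first lesson in section 4.2 is not supported. The speeches show end-of-course attainment. They show neither a gain in rhetoric nor an effect of the seminar, because no rhetoric or message-communication task preceded it and there was no control group. Attainment of criterion 3 remains assessable; how far the course or the seminar produced it does not.

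The consequence is modest. One sentence in the pilot report is affected, and no stated final conclusion depends on it. The larger value lies in the repeat editions, where the same design would leave the same question open.

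This assumes that the figures not reproduced in the text, in particular the schedule (Fig 2) and the diagram of evaluation moments (Fig 3), show no further instrument.

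**What to change.** **For the pilot report.** Replace the first lesson in section 4.2 with: *the speeches were well structured after the seminar; whether this reflects learning was not measured.* This costs nothing.

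**For later editions.** Have all consenting students write the same short timed explanation of palliative care for a lay listener on three occasions: at Moment 1 (for example, by adapting the PCKQ open question), just before the seminar, and at Moment 3. Keep the prompt, length and rubric identical, and score with author and time point removed. The first and last texts bear on the course, the second and last on the seminar. Comparing a short draft with the prepared speech would not serve: the two differ in preparation and form, and scorers could tell them apart. Report the result as change and not as proof of cause while there is no control group.

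**Cost.** About 10 minutes per occasion, or 3 × 10 = 30 minutes per student, and 25 × 3 = 75 short texts to score for a group the size of the pilot's participants. Repeating the task may itself give some practice.

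Two practical points follow from the pilot. Only 12 of 25 (48%) answered at Moment 1, so an emailed baseline at that rate would give at most 12 starting texts. Matching texts over time also needs the improved code system that section 6 already calls for.
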